#### **6.11.5. Unblinding regulations**

If the primary objectives are achieved or the sponsor decides to terminate the research, the data manager will clean up the data and then lock the database. Unblinding can only be performed after the database is locked and the group of participants corresponding to the study number can be revealed.

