#### **6. Study Design**

##### **6.1. Study objective(s)**

##### **6.1.1. Primary objective(s)**

---

➤ **The primary objective of protective efficacy**

1) To evaluate the protective efficacy of the investigational vaccine or placebo in the prevention of symptomatic COVID-19 cases of any severity (Appendix 1) occurring from 14 days after booster vaccination in adults aged 18 and older who have completed 2 or 3 doses of inactivated COVID-19 vaccines.

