### **6.4. Study hypothesis**

The lower limit of the confidence interval for the protection efficacy (vaccine efficacy, VE) against symptomatic COVID-19 cases occurring from 14 days after booster vaccination in adults aged 18 and older is more than 30%.

Null hypothesis(H0): the lower limit of 95% confidence interval for the VE  $\leq 30\%$

Alternative hypothesis(H1): the lower limit of 95% confidence interval for the VE  $> 30\%$

The overall test level of the study is  $\alpha=0.025$ (one-sided).

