#### **6.11.4. Emergency unblinding**

Only in emergencies or when serious adverse events occur, and the information of the investigational product is critical to the clinical treatment or health of the participants, it is necessary to conduct individual emergency unblinding and make relevant records, after the confirmation by the principal investigator and sponsor. The participant with this study number will terminate the study as a dropout, and the investigator will record the reason for termination in the "Vaccination and Follow-up Record Book".

If group adverse events occur or the study needs to be interrupted for any reason, the unblinding could be done in advance with the approval of the sponsor.

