#### **6.11.6. Blind maintenance**

During the implementation of this clinical research, observer blindness should be maintained, that is, the participants, the observers(researchers) of safety or efficacy, and the staff of laboratory test are all blinded. The staff responsible for vaccine management and vaccination are unblinded.

Unblinded staff who are authorized for vaccine management, vaccination, unblinded data management, unblinded quality control(QC), and unblinded monitoring are required to sign a confidentiality agreement and promise not to disclose any information that may cause blindness breaking to other personnel (including the investigators involved, the participants, the staff for serum sample

---

detection, the blinded monitors, QC staffs, and data management staffs, etc.). At the same time, unblinded staff are no longer authorized to participate in other works that may lead to blindness breaking, such as safety observation.

The monitoring and QC works involving vaccine management and vaccination will be completed by unblinded monitors and QC staff.

When the vaccines are transported to the clinical research site, they will be properly managed by the vaccine/drug administrators on site.

Other biological samples such as blood are only marked with the code related to the study number, to ensure that the detection is blinded.

After the study is unblinded, the research at the clinical site will enter into the open stage, but the detection remain blinded. Anyone is forbidden to disclose any information that may cause blindness breaking to the detection agencies to ensure the objectivity of the testing data.

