#### **6.12. Study suspension or termination criteria**

The sponsor reserves the right to suspend/terminate the study at any time. After full consultation with the sponsor and the sponsor's consent, the investigator could suspend or terminate the work of the research center. Reasons for suspending or terminating the study may be, but are not limited to, the following:

- (1) It is clear that the investigational vaccine lacks efficacy;
- (2) The incidence or severity of adverse reactions indicate that there may be potential dangers that may endanger the life of the participants;
- (3) The sponsor suspends or terminates the research voluntarily;
- (4) Suspend or terminate due to regulatory agency requirements.

During the study, if any of the criteria triggering the study suspension occurs, the safety of the investigational vaccine will be assessed by the investigator.

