#### **11.8.3. Interim Analysis**

Not applicable.

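### Emergency-unblinded participants are dropped after their only dose, and the lock rule names neither 162 cases nor day 180 although unblinding opens the site

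*Protocol*

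**What the plan says.** - **Emergency unblinding (6.11.4).** Individual unblinding is limited to emergencies or serious adverse events where knowing the product is critical to care, with confirmation by the principal investigator and sponsor. The consequence is: "The participant with this study number will terminate the study as a dropout".
- **Withdrawal (7.3, 7.4).** Data collected before withdrawal may be used, and adverse events are followed to definite diagnosis, stability or recovery. A participant who becomes pregnant after vaccination need not be withdrawn and stays under observation.
- **Lock and unblinding (6.11.5).** "If the primary objectives are achieved or the sponsor decides to terminate the research, the data manager will clean up the data", followed by lock. "Unblinding can only be performed after the database is locked".
- **After unblinding (6.11.6).** "After the study is unblinded, the research at the clinical site will enter into the open stage"; laboratory testing remains blinded.
- **Objective and hypothesis.** The primary objective (6.1.1) is "To evaluate the protective efficacy of the investigational vaccine or placebo in the prevention of symptomatic COVID-19 cases of any severity". The hypothesis (6.4) concerns "The lower limit of the confidence interval for the protection efficacy (vaccine efficacy, VE) against symptomatic COVID-19 cases" and requires that limit to exceed 30%.
- **Case count and follow-up.** Section 6.5.1 counts cases blind towards a fixed 162. Section 6.6 provides for 162 being reached by day 90 or later, with monthly visits afterwards to day 180. Section 6.7 collects SAEs, AESIs and pregnancies for six months.
- **Stopping (6.12, 11.8.3).** One possible reason for stopping is "It is clear that the investigational vaccine lacks efficacy". The interim analysis section reads "Not applicable".

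**The concern.** Three rules need repair.

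**Dropout after emergency unblinding.** There is no further dose to withhold, so ending participation protects nobody and only removes later observation. The people removed are by rule those with emergencies or serious events. If such events differ between arms, so does the loss, and it falls on endpoints with few events.

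**An unnamed lock trigger followed by an open site.** Section 6.11.5 does not say what achieving the objectives means, and nothing delays lock until the last day-180 visit. Once the site is open, known allocation can influence symptom reporting (which prompts swabbing under 6.6), severity grading (Appendix 1) and causality assessment (11.4.4).

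**A stopping reason with no analysis behind it.** Section 6.12 allows stopping for lack of efficacy, but no interim analysis exists and no one is named to judge it.

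**Working it through.** **1. Emergency unblinding.** The sections side by side:
- 9.3: one dose, on day 0.
- 6.11.4: the unblinded participant leaves as a dropout.
- 7.4: events already present are followed to an outcome; scheduled visits stop.
- 7.3(3): a vaccinated participant who becomes pregnant stays in follow-up.

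The event that prompted unblinding is therefore kept. New SAEs, AESIs and COVID-19 cases up to day 180 are not systematically collected. The documents give no expected number of emergency unblindings, so the loss cannot be quantified.

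**2. Two readings of the lock trigger.**
- Against 6.4, achieving the objective means a lower VE limit above 30%. That needs group data, which 6.11.5 releases only after lock, so the rule is circular.
- Against 6.1.1 and 6.5.1, it means that the evaluation has become possible, that is, 162 cases counted blind. That is workable.

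Section 6.11.5 does not choose between them.

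**3. Reproducing the 162 cases.** Inputs from 6.5.1: margin VE 30%, expected VE 60%, 1:1 allocation, one-sided 0.025, power 90%, incidence 9%. Given the total number of cases, the vaccine-arm share is binomial:
- under VE 30%: p0 = 0.7/1.7 = 0.4118
- under VE 60%: p1 = 0.4/1.4 = 0.2857

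The exact test keeps power at or above 90% at every count from 160 upward (checked to 259). At 162 cases, success requires at most 54 in the vaccine arm; exact alpha is 0.0247 and power 92.2%. Per group, 162/(0.09 + 0.09 × 0.4) = 162/0.126 = 1,286, as stated. Then 1,286/0.8 = 1,608, against 1,600 planned. The protocol's figures stand.

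**4. When could 162 cases occur?** Assumptions: 9% is the placebo risk over days 14 to 180 (166 days), the rate is constant, and everyone is vaccinated at the same time. Day of the 162nd case = 14 + 166 × 162/(0.126 × participants per arm).

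| Participants counted | Expected cases by day 180 | Day of 162nd case | Share of 180 days remaining |
|---|---|---|---|
| 3,200 (1,600 per arm) | 201.6 | 147 | 33/180 = 18% |
| 2,560 (1,280 per arm) | 161.3 | 181 | none |
| Day 90, the earliest step-down in 6.6 | – | 90 | 90/180 = 50% |

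Data cleaning and blind review (11.7) would delay unblinding and shorten the open period. Staggered enrolment would lengthen it for participants vaccinated last. The protocol gives no duration for either.

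**The case against.** The strongest defence is that the text, read as a whole, works. The primary objective is to evaluate efficacy, cases are counted blind towards a number that cannot be changed, no interim analysis is planned, and unblinding at the end follows lock. This stands as far as it goes: 6.11.5 is ambiguous, not certainly dependent on the result.

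The defence also holds on these points:
- Stopping for lack of efficacy cannot raise the type I error of a superiority claim, 6.12 gives it only as a possible reason, and evidence from outside the trial could satisfy it.
- Primary data would already be locked before any open stage. Severe disease rests partly on measured criteria such as respiratory rate and oxygen saturation, with expert committee assessment, and laboratory testing stays blinded.
- Emergency unblinding should be rare, and 7.4 keeps the triggering event.

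It does not answer that 6.11.4 ends observation for no stated reason, that 6.11.6 expects work at an open site, or that no section holds lock until the last day-180 visit. Section 11.2.8 ties site closure to lock but does not fix when lock falls.

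**Conclusion.** This should be fixed. Followed as written, the dropout rule loses later events in a selected group. The lock and open-stage rules together permit open-label collection of secondary efficacy and six-month safety data, though only if 162 cases are reached before the last day-180 visit. Section 6.6 contemplates that, but it is not certain. Under the assumptions above, the open share is about 18% or nothing.

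A reader might infer more than the documents support:
- **That the one-sided 0.025 level is broken.** Unadjusted looks would inflate it (exact alpha 0.0385 with looks at 81 and 162 cases, 0.0458 with looks at 54, 108 and 162), but the protocol plans no such looks. The single analysis has alpha 0.0247.
- **That lock certainly depends on the efficacy result.** The wording of 6.1.1 and the blinded count in 6.5.1 allow a reading that does not.
- **That about half of follow-up would be open-label.** That requires 162 cases by day 90 and is the worst case.

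**What to change.** - **6.11.4:** keep emergency-unblinded participants in efficacy and safety follow-up to day 180 unless they withdraw themselves, and flag them for a sensitivity analysis. The conditions for emergency unblinding need not change.
- **6.11.5:** state that the single primary lock occurs when the blinded count of primary cases reaches 162, or at the last day-180 visit if it does not. State that the remaining six-month data are locked after that visit.
- **6.11.6:** keep participants, site staff, and endpoint and safety assessors masked until the last day-180 visit. Only a separate analysis team is unblinded earlier.
- **6.12 and 11.8.3:** reconcile them by stating who may judge lack of efficacy and on what evidence, given that no interim analysis is planned.

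The cost is a wording amendment, a firewall around the analysis team until the last visit, and continued contact with a presumably small number of emergency-unblinded participants. The sample size and the case target do not change.

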#### **6.11.6. Blind maintenance**

During the implementation of this clinical research, observer blindness should be maintained, that is, the participants, the observers(researchers) of safety or efficacy, and the staff of laboratory test are all blinded. The staff responsible for vaccine management and vaccination are unblinded.

Unblinded staff who are authorized for vaccine management, vaccination, unblinded data management, unblinded quality control(QC), and unblinded monitoring are required to sign a confidentiality agreement and promise not to disclose any information that may cause blindness breaking to other personnel (including the investigators involved, the participants, the staff for serum sample

---

detection, the blinded monitors, QC staffs, and data management staffs, etc.). At the same time, unblinded staff are no longer authorized to participate in other works that may lead to blindness breaking, such as safety observation.

The monitoring and QC works involving vaccine management and vaccination will be completed by unblinded monitors and QC staff.

When the vaccines are transported to the clinical research site, they will be properly managed by the vaccine/drug administrators on site.

Other biological samples such as blood are only marked with the code related to the study number, to ensure that the detection is blinded.

After the study is unblinded, the research at the clinical site will enter into the open stage, but the detection remain blinded. Anyone is forbidden to disclose any information that may cause blindness breaking to the detection agencies to ensure the objectivity of the testing data.

#### **6.12. Study suspension or termination criteria**

The sponsor reserves the right to suspend/terminate the study at any time. After full consultation with the sponsor and the sponsor's consent, the investigator could suspend or terminate the work of the research center. Reasons for suspending or terminating the study may be, but are not limited to, the following:

- (1) It is clear that the investigational vaccine lacks efficacy;
- (2) The incidence or severity of adverse reactions indicate that there may be potential dangers that may endanger the life of the participants;
- (3) The sponsor suspends or terminates the research voluntarily;
- (4) Suspend or terminate due to regulatory agency requirements.

During the study, if any of the criteria triggering the study suspension occurs, the safety of the investigational vaccine will be assessed by the investigator.

#### **6.13. Confidentiality agreement and privacy of the participants**

The investigators shall undertake to keep confidential to third parties any confidential information obtained from the sponsors or investigational products, or

---

provided or disclosed in the current contract, and to use such information within the agreed scope of the agreement.

As long as the sponsor has a reasonable and justifiable reason to require the investigator to maintain the confidentiality of the agreement, the agreement should be independent and valid for the duration of the contractual relationship between the two parties.

The investigators must ensure the privacy of the participants in the clinical research. In all the documents submitted to the sponsor, the identity of the participants can only be determined by the subject codes of the clinical research, and the names of the participants cannot be indicated. The investigators must properly keep the names and addresses of the participants and the enrollment form corresponding to the subject codes. These enrollment forms are kept strictly confidential by the investigator and cannot be submitted to the sponsor.

#### **6.14. Study Duration**

All participants will be in the study for about 6-7 months.

### **7. Study population**

#### **7.1. Inclusion criteria**

Participants must meet all the following inclusion criteria:

- (1) Both male and female adults aged 18 years and above who can provide their identification;
- (2) Understand the contents of the ICF and the vaccine for this vaccination, sign the ICF, and have the ability to use a thermometer, scale, and fill in the diary card and contact card as required;
- (3) Be able to communicate well with the researcher and understand and comply with

---

the requirements of this study;

(4) Participants must have received 2 or 3 doses of SARS-CoV-2 inactivated vaccine, with the last dose received at least 6 months before enrolment.

(5) Healthy participants or participants with mild underlying disease [in a stable state without exacerbation (no admission to hospital or no major adjustment to treatment regimen, etc.) for at least 3 months before enrollment in this study].

(6) For female participants: without childbearing potential (amenorrhea for at least 1 year or documented surgical sterilization) or not in pregnancy or lactation and have used effective contraception (e.g., intrauterine or implantable contraceptive devices, oral contraceptives, injectable or buried contraceptives, sustained-release topical contraceptives, intrauterine devices (IUDs), condoms (for males), diaphragms, cervical caps, etc.) for the past 14 days before the first dose of vaccine (provide negative pregnancy certificate within 48 hours);

(7) Negative results within 48 hours for SARS-CoV-2 pathogenicity testing (RT-PCR).

## **7.2. Exclusion criteria**

Participants meeting any of the following criteria will be excluded from the study.

(1) Abnormal vital signs that are clinically significant (e.g., blood pressure that is still abnormal after control);

(2) COVID-19 infection in the last 6 months or use of any COVID-19 prophylactic medication other than 3 doses of inactivated SARS-CoV-2 vaccine (e.g., a history of vaccination with any other non-inactivated SARS-CoV-2 inactivated vaccine, marketed or unlisted, or vaccination with 1 or 4 doses of inactivated SARS-CoV-2 vaccine)

(3) A history of Severe Acute Respiratory Syndrome (SARS), Middle East Respiratory Syndrome (MERS), or other coronavirus infections at any time.

(4) Axillary temperature  $\geq 37.3^{\circ}\text{C}$  detected on the day of vaccination or fever within the last 24 hours (axillary temperature  $\geq 37.3^{\circ}\text{C}$ /oral temperature  $\geq 37.5^{\circ}\text{C}$ );

- 
- (5) A history of severe allergic or allergic reactions to vaccines or drugs, e.g., urticaria, severe skin eczema, dyspnea, laryngeal edema, angioneurotic edema, etc.
  - (6) Any other licensed vaccines given within 28 days before study vaccination;
  - (7) Participation in a clinical study of other drugs within 28 days before vaccination or planned participation within 6 months after vaccination;
  - (8) Have an inherited bleeding tendency or coagulation disorder (eg: Cytokine deficiency, coagulopathy, or thrombocytopenia), or a history of severe bleeding;
  - (9) Diseases affecting the functioning of the immune system (e.g., cancer, except basal cell carcinoma of the skin), congenital or acquired immunodeficiencies (e.g., HIV infection), uncontrolled autoimmune diseases, etc., based on a known medical history or diagnosis;
  - (10) Asplenia or functional asplenia;
  - (11) Long-term use (continuous use for  $\geq 14$  days) of immunosuppressants or other immunomodulatory drugs (eg, corticosteroids: prednisone or equivalent; interferon, etc.) within 6 months before study vaccination. Topical medications (e.g., ointments, eye drops, inhalers, or nasal sprays) are permitted and should not exceed the dose recommended in the instructions;
  - (12) Receipt of immunoglobulins and/or blood products within 3 months before study vaccination;
  - (13) Suspected or known alcohol dependence or drug abuse;
  - (14) Participants were deemed unsuitable for participation in this study based on the investigator's assessment.

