| Exclusion criteria | 
Participants meeting any of the following criteria will be excluded from the study.
 
(1) Abnormal vital signs that are clinically significant (e.g., blood pressure that is still abnormal after control);
 
(2) COVID-19 infection in the last 6 months or use of any COVID-19 prophylactic medication other than 3 doses of inactivated SARS-CoV-2 inactivated vaccine (e.g., a history of vaccination with any other non-inactivated SARS-CoV-2 inactivated vaccine, marketed or unlisted, or vaccination with 1 or 4 doses of inactivated SARS-CoV-2 vaccine)
 
(3) A history of Severe Acute Respiratory Syndrome (SARS), Middle East Respiratory Syndrome (MERS), or other coronavirus infections at any time.
 
(4) Axillary temperature <math>\geq 37.3^{\circ}\text{C}</math> detected on the day of vaccination or fever within the last 24 hours (axillary temperature <math>\geq 37.3^{\circ}\text{C}</math>/oral temperature <math>\geq 37.5^{\circ}\text{C}</math>);
 
(5) A history of severe allergic or allergic reactions to vaccines or drugs, e.g., urticaria, severe skin eczema, dyspnea, laryngeal edema, angioneurotic edema, etc.
 
(6) Any other licensed vaccines given within 28 days before study vaccination;
 
(7) Participation in a clinical study of other drugs within 28 days before vaccination or planned participation within 6 months after vaccination;
 
(8) Have an inherited bleeding tendency or coagulation disorder (eg: Cytokine deficiency, coagulopathy, or thrombocytopenia), or a history of severe bleeding;
 |

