## **1. Study Title**

A Single-Center, Randomized, Blinded, Placebo-Controlled Clinical Study to Evaluate the Efficacy, Safety, and Immunogenicity of a SARS-CoV-2 Variant (Omicron BA.5) mRNA Vaccine (LVRNA012) Vaccine Administered as 1 Dose in adults Aged 18 Years and Older Who Have Completed 2 or 3 Doses of SARS-CoV-2 inactivated Vaccine.

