## **11.8. Statistical analysis**

### **11.8.1. Analysis Sets**

#### **➤ Analysis set of efficacy**

**Full analysis set of efficacy(E-FAS):** Include all subjects who followed the intention-to-treat (ITT) principle, entered randomization and completed vaccination, and had at least one case surveillance follow-up after vaccination.

**Modified full analysis set of efficacy(E-mFAS):** It is a subset of E-FAS and includes all subjects who completed vaccination, had negative baseline nucleic acid results, and had at least 1 case surveillance follow-up 14 days after vaccination. Among them, COVID-19 cases with positive nucleic acid or antigen test or confirmed diagnosis within 14 days from enrollment to vaccination will also be excluded from this analysis set.

**Per protocol set of efficacy(E-PPS):** It is a subset of E-mFAS, including all subjects who did not violate the inclusion/exclusion criteria, completed vaccination, had negative baseline nucleic acid results, and had at least one case surveillance follow-up 14 days after vaccination, and did not violate the protocol. Among them, COVID-19 cases with positive nucleic acid or antigen test or confirmed diagnosis within 14 days from enrollment to vaccination will also be excluded from this analysis set.

Cases of E-mFAS and E-PPS are counted from 14 days after vaccination and are

---

mainly used for the evaluation of the main protective efficacy of the vaccine. Among them, E-mFAS is the main analysis set for the evaluation of protective efficacy in this study. E-FAS was used to evaluate the protective efficacy after vaccination.

➤ **Analysis set of immunogenicity**

**Full analysis set of immunogenicity(I-FAS):** Include all subjects in the immunization subgroup who follow the ITT principle, enter randomization and complete vaccination, and have valid antibody data before vaccination.

**Per protocol set of immunogenicity(I-PPS):** Include all subjects in the immunization subgroup who did not violate the inclusion/exclusion criteria, completed the vaccination, had blood samples collected at the evaluation time points, and had valid antibody data. The immunogenicity analysis sets were defined for the immunogenicity evaluation of each group at 7 days, 14 days, and 28 days after vaccination respectively.

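### Exclusion criterion 2 permits only 3 prior inactivated doses, so on its wording it excludes the 2-dose recipients that inclusion criterion 4 and the title admit

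*Protocol*

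**What the plan says.** The population is defined by prior doses in several places, and these agree. The title (section 1) describes adults "Who Have Completed 2 or 3 Doses of SARS-CoV-2 inactivated Vaccine". Inclusion criterion 4 (section 7.1) reads: "Participants must have received 2 or 3 doses of SARS-CoV-2 inactivated vaccine, with the last dose received at least 6 months before enrolment". Section 5 and the allocation table in section 6.5.2 give the same 2-or-3-dose range.

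Exclusion criterion 2 (section 7.2) differs. Besides recent infection, it excludes "use of any COVID-19 prophylactic medication other than 3 doses of inactivated SARS-CoV-2 vaccine". Its examples in brackets include "vaccination with 1 or 4 doses of inactivated SARS-CoV-2 vaccine". The synopsis copy has the same limit: "prophylactic medication other than 3 doses of inactivated SARS-CoV-2 inactivated vaccine".

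Two other parts of the protocol give the criterion its force. Section 11.2.1, steps 2 and 3, has staff confirm the vaccination record and enrol only people who meet the inclusion criteria and none of the exclusions. Section 11.8.1 restricts E-PPS to "all subjects who did not violate the inclusion/exclusion criteria", among other conditions, and puts the same condition on I-PPS. E-mFAS, the main efficacy set, has no such condition.

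**The concern.** The protocol has an inclusion criterion and an exclusion criterion that give opposite answers for the same person, and no clause says which prevails. Eligibility criteria are applied one by one at screening, and meeting any single exclusion is enough to bar a person. A 2-dose recipient satisfies section 7.1(4) and is barred by section 7.2(2).

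Two things are at stake. One is whether the enrolled population matches the one in the title. The other is whether 2-dose participants who are enrolled remain in the per-protocol sets. Section 8.2 adds an administrative burden: deviations that may affect eligibility must be reported promptly to the ethics committee and the sponsor, so each enrolled 2-dose participant is arguably reportable.

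**Working it through.** The point turns on wording and disputes none of the plan's figures. The check is to put each possible dose history through the criteria as written.

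**Step 1: what the exclusion covers.** The exception in section 7.2(2) is itself a vaccine course. The criterion therefore treats prior vaccination as a form of prophylactic use, and the only course it spares is 3 inactivated doses. The examples confirm that the number of doses alone can trigger the exclusion, including a number below 3.

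**Step 2: each dose count in turn.** Other criteria are assumed to be satisfied.

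| Prior inactivated doses | Inclusion 7.1(4) | Governing phrase of 7.2(2) | Named in the 7.2(2) examples? | Literal result under 11.2.1 |
|---|---|---|---|---|
| 1 | not met | excluded | yes | not enrolled |
| 2 | met | excluded | no | not enrolled |
| 3 | met | not excluded | no | enrolled |
| 4 | not met | excluded | yes | not enrolled |

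The two criteria conflict only in the 2-dose row. In that row the governing phrase also sits badly with its own examples, which name the counts on either side of the 2-to-3 range and leave out 2.

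**Step 3: consequences by route.**

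- *Sites apply the exclusion literally.* No 2-dose recipients enter. Every analysis set then describes 3-dose recipients only, although the title and population statement say 2 or 3.
- *Sites follow section 7.1(4) and enrol them.* Each one has met a written exclusion. Under section 11.8.1 they fail the eligibility condition of E-PPS and I-PPS. E-FAS, E-mFAS, the immune persistence set and the safety set have no eligibility condition, so these participants stay in those sets.

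**Step 4: can a size be given?** If 2-dose recipients supplied a share s of the cases, a literal E-PPS would keep a fraction 1 − s of them. The protocol gives no value or range for s and states no power for E-PPS. The planning figures do not depend on dose history: 162 / (0.09 × 1.4) = 1,285.7, which rounds up to the stated 1,286 per group. The calculation stops there.

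**The case against.** The strongest reply is that the protocol already shows what was meant. Naming 1 and 4 doses makes sense only if 2 and 3 are both acceptable, and every statement of the population says so. Staff reading both lists together would probably enrol 2-dose recipients, and the blinded data review (section 11.8.1) could settle set membership sensibly. This stands as evidence of intent and makes a drafting slip the likely explanation. It does not remove the defect. Illustrative examples do not override the phrase they illustrate, and the limit appears in both places where the exclusions are listed. The Introduction's emphasis on a fourth dose after three also makes a 3-dose-only reading plausible to screening staff. Leaving the matter to the review meeting means asking it to set aside a written criterion or remove part of the target population.

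A reader might go further and infer that the trial cannot support a conclusion for 2-or-3-dose recipients. The documents support that only if sites refuse 2-dose recipients. If they are enrolled, the primary E-mFAS result includes them.

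A reader might also infer a definite loss of power. The documents do not support that either. The 2-dose share is unknown, and E-PPS is a supporting set with no planned power. If 2-dose recipients are not enrolled at all, section 6.5.1 still fixes the required number of cases and allows enrolment to be increased.

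Nor does the conflict reach every objective: the secondary immunogenicity objectives in section 6.1.2 do not restate the dose history.

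**Conclusion.** The contradiction is certain on the text: section 7.2(2) and its synopsis copy exclude a group that section 7.1(4), the title, section 5 and the allocation table admit. It is probably a slip, but it sits in a rule applied to about 3,200 people at screening.

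Its reach is limited. Either 2-dose recipients are not enrolled and the stated population is not covered, or they are enrolled and a literal reading drops them from E-PPS and I-PPS only. The second route requires the criterion to be read loosely at enrolment and literally at the blinded review. The primary E-mFAS analysis is not affected for anyone enrolled. No numerical effect can be given, because the share of 2-dose recipients is not in the protocol. It should be corrected because it is clear-cut and cheap to put right, not because a loss to the primary analysis has been shown.

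**What to change.** Reconcile exclusion criterion 2, in section 7.2 and in the synopsis, with inclusion criterion 4 and the stated 2-or-3-dose population, so that the exclusion no longer captures people the inclusion criterion admits. The examples in brackets already fit that population and need not change. Do this before per-protocol membership is decided at the blinded review. If 2-dose recipients have been enrolled by then, record before unblinding that their dose history does not count as an eligibility violation for E-PPS or I-PPS.

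The text change is a few words in two places, with no effect on sample size, endpoints or analysis methods. The process cost is somewhat larger: section 14.2 requires the sponsor's prior written approval and ethics approval before an amendment takes effect.
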